### Researchers

The acupuncturists who deliver treatments for the four groups are registered with the Ministry of Health of the People’s Republic of China as Chinese medicine practitioners and have more than 6 years of clinical experience. In addition, two supervisory data collectors and analysts who do not know the random assignment protocol will monitor the whole experiment. What is more, people who are responsible for recruiting participants, researchers, outcome assessors, and statisticians in the trial will receive special training regarding the purpose and standard procedure of the project before the trial begins strictly.

### Informed consent

Each patient will be informed of the study protocol information regarding random allocation, possible benefits and risks, and so on. Then, we will provide sufficient time for all patients to decide whether to participate in the trial. Only if they voluntarily sign the informed consent will they be randomized to a group. Moreover, the patients will be free to withdraw from the study at any time without a specific reason and any penalty or loss of benefits. However, we will attempt to record the reason for withdrawal and encourage the participant to remain in the study if possible.

### Safety assessment

Adverse events (AEs) caused by acupuncture such as pain, bleeding, fainting, allergy, or other severe events will be processed immediately and recorded in detail in the case report forms (CRF). Participants with mild and moderate AEs will be treated for their symptoms and closely monitored as necessary by the researcher, while severe AEs will be reported to the Research Ethics Committee, which will provide medical advice to the research team within 48 h, and the Research Ethics Committee will determine whether a termination of the trial is required. Patients may choose to withdraw from the trial due to any AE.

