**Assessments**								
WOMAC		X				X	X	X
VAS		X				X	X	X
AIMF2-SF		X				X	X	X
BAI		X				X	X	X
BDI		X				X	X	X
CEQ		X						
Adverse events		X	X	X	X	X	X	X

Qualification screening and informed consent will be completed before the assignment. After allocation, each patient will be treated within 4 weeks. The evaluation will be performed at baseline and weeks 4, 8, and 12 respectively after randomization. Adverse events will be recorded on the case report form at any time during treatment

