### Discontinuation criteria and modification

During the trial period, patients with KOA who meet the following criteria will be excluded from the study: (1) protocol violation such as taking analgesic without permission or receiving additional treatment that may interfere with the efficacy of acupuncture, (2) withdrawal of consent for study participation because the patients do not wish to continue, (3) missing more than 4 of 20 acupuncture treatment sessions, and (4) occurrence of a serious adverse event that the doctors consider should lead to termination of trial participation.

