### Blinding

Due to the operation characteristics of acupuncture, acupuncturists will be asked to apply the different methods of stimulation, they will not be blinded to treatment allocation for the different locations in each group. However, participants will be blinded to group assignment, and they will be informed that there are four methods of acupuncture treatment provided in this study and will accept one of them in a separate compartment. Each participant will be treated separately to prevent any exchange of study information. In addition, the outcome assessors, data recorders, acupuncturists, and statisticians will all operate independently; the randomization staff and acupuncturist will know the allocation information, while the outcome assessor and statisticians will stay blind to this information throughout the study. Unblinding will not be done until the completion of data analysis, and after the data analysis, we will have a blinded interpretation of the study results to minimize misleading data interpretation. In short, we will implement the three separation principles of researchers, operators, and statisticians for the sake of reducing the risk of bias.

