### Data collecting and monitoring

The governance of this study will be carried out by the trial steering committee (TSC), composed of the primary investigators and statisticians, who will oversee the entire study conduct to ensure that all researchers participating in this study are following the proposed protocol. A monthly meeting will be conducted where the TSC can supervise the progress and the data quality of this study and share suggestions if problems occur. The Ethics Committee will hold an annual meeting to monitor the implementation of the entire trial.

In this study, the data that includes observation time points, scanning time points, outcome measures, adverse events, and safety evaluations will be collected at baseline and weeks 4, 8, and 12 after the intervention using the case report form. And a special assistant will be responsible for reviewing data integrity, accuracy, and consistency. Patients will be assigned to a quiet room for psychological factor assessments. In order to ensure the consistency of source data, all the scales will be assessed by the same researcher during the study. Meanwhile, the research data will be input into EpiData electronic database. For ensuring the accuracy of data entry, data will be entered independently by two researchers, and then the discordances will be resolved by tracing source data.

When the trial is completed, the database will be locked by the data management team, after which the researchers can no longer modify the data. Both paper files and electronic documents will be preserved for at least 5 years after publication. If readers and reviewers have any questions, they can contact the corresponding author for access to the original data. Patient information will remain anonymous, including name, ID number, and telephone number.

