## Discussion

Acupuncture, as a complementary and alternative therapy, is widely used in patients with KOA with the advantages of high safety and fewer side effects, and it becomes increasingly accepted in the world. There is also a growing number of scholars studying on acupuncture for KOA, especially since 2015 when the number of studies has risen sharply [29]. These studies include traditional MA, EA, acupuncture on sensitive acupoints, and thread embedding acupuncture, which fully prove the effectiveness of acupuncture in the treatment of KOA [30–32]. In addition, some scholars have found that the 3 sessions per week of acupuncture work better in improving knee pain and dysfunction than 1 session per week of acupuncture and the benefit of 3 sessions per week persists throughout follow-up [33]. However, the acupuncture treatment method for KOA is still a research topic, particularly the difference in the efficacy of different acupuncture treatments for KOA needs further study. So, this trial is designed as an RCT. The completion of this trial will provide detailed and accurate evidence of the efficacy and safety of MA, EA, and WA on KOA. The advantages of the trial design are shown in the following aspects.

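### The safety section sends only adverse events attributed to acupuncture to the case report form, other sections carry no such filter, and the recording window is stated in three ways

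*Protocol article*

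**What the plan says.** **What is recorded.** The Safety assessment section says that "Adverse events (AEs) caused by acupuncture such as pain, bleeding, fainting, allergy, or other severe events" are to be handled at once and entered in detail in the case report form. It names a researcher for the follow-up of mild and moderate events. It does not say who decides that an event was caused by acupuncture. Table 1 lists adverse events without a causal condition, and so does Data collecting and monitoring.

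**When.** The Table 1 row reads "Adverse events X X X X X X X", with marks at week 0, weeks 1 to 4, week 8 and week 12. The footnote to the same table says "Adverse events will be recorded on the case report form at any time during treatment". Data collecting and monitoring says that the data, adverse events included, "will be collected at baseline and weeks 4, 8, and 12 after the intervention using the case report form".

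**Who knows the arm.** Under Blinding, "the randomization staff and acupuncturist will know the allocation information, while the outcome assessor and statisticians will stay blind to this information".

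**Which terms.** In Safety assessment, "severe AEs will be reported to the Research Ethics Committee". In Discontinuation criteria and modification, a participant leaves the trial on "occurrence of a serious adverse event that the doctors consider should lead to termination of trial participation". Neither term is defined.

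**What is promised.** The Discussion says that the trial will give "detailed and accurate evidence of the efficacy and safety of MA, EA, and WA on KOA".

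**The concern.** A causal condition placed before recording works as a filter. An event that nobody attributes to the needling need not reach the case report form, and no later analysis can bring it back. If the filter passes a different share of events in different arms, the recorded rates differ for a reason unrelated to safety.

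This design leaves room for that. The person giving the treatment sees deep insertion with manipulation in the manual arm, current in the electro-acupuncture arm, burning moxa in the warm arm, and shallow needling without manipulation in the sham arm. Bleeding, fainting and needling pain would be expected mainly during these sessions. The Group C section also asks for a check for blisters and bleeding when the needles come out. No such check is written for the other three arms, although bleeding is a listed adverse event and the skin is pierced in every arm.

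The window raises a separate question: whether events after week 4 are to be collected at all. At stake is the quality of the arm-by-arm safety evidence. The primary outcome, WOMAC at week 4, is not affected.

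**Working it through.** The plan gives no adverse event rate and no attribution rate, so there is no figure of its own to reproduce. The check is a comparison of the passages, followed by an illustration on assumed inputs.

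**1. Recording rule**

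| Place | Events covered |
|---|---|
| Safety assessment | those caused by acupuncture |
| Table 1, row and footnote | adverse events, no condition |
| Data collecting and monitoring | adverse events, no condition |

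Staff who follow the first line could omit events that staff who follow the other two would record.

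**2. Recording window**

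| Place | Window |
|---|---|
| Table 1 row | weeks 0, 1, 2, 3, 4, 8, 12 (7 marks) |
| Table 1 footnote | any time during treatment, which lasts 4 weeks |
| Data collecting and monitoring | baseline, weeks 4, 8, 12 (4 time points) |

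If the footnote is taken as the limit, 12 − 4 = 8 weeks of follow-up are not covered. The data collection text covers follow-up but omits the marks at weeks 1, 2 and 3 (7 − 4 = 3). It also counts from the intervention, whereas the footnote counts assessments from randomization.

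**3. What a causal filter can do (all inputs assumed)**

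Recorded rate = true rate × probability that the event is attributed to acupuncture. With equal true rates, the true rate cancels:

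recorded risk ratio = (attribution in active arm) / (attribution in sham arm)

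| Attribution, active / sham | Recorded at true 10% | At true 20% | At true 30% | Risk ratio |
|---|---|---|---|---|
| 90% / 90% | 9% / 9% | 18% / 18% | 27% / 27% | 0.90/0.90 = 1.00 |
| 90% / 70% | 9% / 7% | 18% / 14% | 27% / 21% | 0.90/0.70 = 1.29 |
| 90% / 50% | 9% / 5% | 18% / 10% | 27% / 15% | 0.90/0.50 = 1.80 |

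With 50 patients per arm and a true rate of 20%, 50 × 0.20 = 10 patients per arm have an event. The middle row then records 10 × 0.90 = 9 against 10 × 0.70 = 7, and the last row 9 against 5. Unequal searching acts in the same way, as a further multiplier. The filter creates a false difference only if attribution or searching differs between arms. The documents give neither, so neither the presence nor the size of a bias can be derived from them.

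**4. Severe and serious**

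The severity term, set against mild and moderate, triggers the report to the ethics committee. The seriousness term, together with the doctors' judgement, triggers a participant's exit. These are two actions, each with one trigger. With neither term defined, a reader cannot tell whether they denote the same events.

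**The case against.** The strongest reply is that Safety assessment is a handling rule for needling events, not a rule that excludes others. Table 1 and Data collecting and monitoring schedule adverse events without a condition, so all events may be collected anyway. Likewise, the footnote does not say *only*. It can be read as continuous recording in the treatment weeks, added to the scheduled visits at weeks 8 and 12. Both readings are possible. The text does not settle either, and the one section devoted to safety carries the condition. Staff who follow it could leave unattributed events off the form for good. This is a conflict within the stated text, not detail that a condensed article leaves to the full protocol.

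Four stronger readings are tempting, and the objection to each stands:

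- *Unblinded staff judge causality.* No section names the assessor. The acupuncturists know the arm, but the blinding status of the researcher in Safety assessment is not given, and the supervisory data collectors are said not to know the assignment.
- *The safety comparison is biased.* The documents support a risk only. The sham needles also pierce the skin, so events there can be attributed to needling too. The Discussion promises evidence on safety. Safety is not among the listed outcomes, and the Statistical analysis section names no between-arm test of adverse events.
- *Late events will be missed.* The Table 1 row and the data collection section both schedule collection at weeks 8 and 12.
- *Two reporting rules conflict.* Only Safety assessment states a reporting trigger. The other term governs leaving the trial, and two actions may have different criteria.

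**Conclusion.** The point holds as an inconsistency in how adverse events are to be recorded, with a resulting risk of differential ascertainment. Three things are on the page: a causal condition in one section that two other places lack, with no assessor named; an active check written for one arm out of four, in a trial whose acupuncturists know the allocation; and three different statements of the recording window. The size is unknown. Across the assumed range the recorded risk ratio runs from 1.00 (equal attribution, no distortion) to 1.80 (90% against 50%). These figures show the mechanism and predict nothing about this trial. The severity and seriousness wording is loose terminology that needs reconciling, not a proven contradiction. A change is worth making because it is cheap and because events left off the form cannot be recovered.

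**What to change.** 1. In Safety assessment, drop the causal condition on recording. Record every adverse event in all four arms over the Table 1 window, week 0 to week 12, regardless of cause.
2. Ascertain events in the same way in each arm, with the same questions and checks at the same times.
3. Make relatedness a separate field on the case report form, completed after the event is recorded, and state who completes it and whether that person knows the arm.
4. Report all events and related events by arm.
5. Align the Table 1 footnote, Safety assessment, and Data collecting and monitoring with the Table 1 row.
6. The sponsor should reconcile the terms *severe* (ethics reporting) and *serious* (discontinuation) and define each. Which criterion should govern which action is for the sponsor to decide.

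The cost is protocol wording, one field on the form and slightly more adverse event data entry. Sample size and the primary analysis do not change.

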### Interventions

There are 4 groups in this trial, which are group A (MA group), group B (EA group), group C (WA group), and group D (SA group). When experimenting, it is suggested that the patients do not use other methods for the treatment of KOA in addition to the experimental scheme.

#### Group A

Subjects assigned to group A will be treated with MA for 4 weeks. The acupoints used include GB34 (Yanglingquan), SP9 (Yinlingquan), ST35 (Dubi), and EX-LE4 (Neixiyan) (Fig. 2). At the same time, depending on the patient’s condition, two ashi points (the point where the patient feels most pain) can be added. The specific operation method is as follows: after the patients maintain a comfortable position, the acupuncturist will disinfect the skin with 75% alcohol, and use a sterile needle (0.25 mm in diameter, 40 mm in length, Huatuo, Suzhou, China) to the acupuncture points. Needles will be making an optimum insertion into the skin of 21~26 mm. During the acupuncture operation, the acupuncturist will adopt the method of even reinforcing-reducing, while the rotation angle is 90~180°, the lifting amplitude is 0.3~0.5cm and the frequency is 60~90 times/min. After the *deqi* sensation (including soreness, numbness, distention, and heaviness) is obtained, the needle will be retained for 30 min in each session and manipulated every 10 min with intermittent stimulation for maintaining the *deqi* sensation. The needle will be stimulated twice and the manipulation of each acupoint will last for 10 s. MA treatment will be applied once a day, 5 sessions per week for 4 consecutive weeks, and rest for 2 days between treatments.

**Fig. 2 Fig2:**
[figure not shown]
The picture of acupuncture points

#### Group B

In group B, subjects will be treated with EA for 4 weeks. The acupoints and acupuncture operation are the same as the MA group, but after *deqi*, an electrical apparatus (HANS-200A acupoint nerve stimulator, Nanjing Jisheng Medical Co, Ltd) will be connected. When both alligator clips are connected to paired needles, it produces electric currents to stimulate acupoints. The electric wave mode will be the dense-sparse wave; sparse wave and dense wave appear alternately, each wave lasting for 1.5 s to avoid body adaptation caused by the continuous output of a single waveform. The power of the electric current will be adjusted to make each acupoint feel the electric stimulation but still comfortable during the treatment process. The needle will be retained for 30 min in each session. EA treatment will be applied once a day, 5 sessions per week for 4 consecutive weeks, and rest for 2 days between treatments.

#### Group C

In group C, subjects will be treated with WA for 4 weeks. The acupoints, location, and acupuncture operation will be the same as those described for the MA group. After *deqi*, acupuncturists will insert a piece of moxa pillar (3 cm) into the end of the needle, and light the tip of the moxa pillar, when the moxa pillar burning is completed, the acupuncturist will remove the ashes. When the time reaches 30 min, the acupuncturist will remove the acupuncture needles and check thoroughly for any possible blisters or bleeding. WA treatment will be applied once a day, 5 sessions per week for 4 consecutive weeks, and rest for 2 days between treatments.

#### Group D

In group D, the non-acupoints used in the SA are all located 1cm away from the outer side of the midline of the lower extremity of the six acupuncture points selected in the MA group. Patients in the SA group will undergo the same procedures as those in the MA group. The needle depth is 1~2mm, and the needle will be directly retained for 30 min without any manipulation in the whole procedure to avoid the *deqi* sensation as much as possible. The SA treatment will be applied once a day, 5 sessions per week for 4 consecutive weeks, and rest for 2 days between treatments.

### Outcome assessments

If only one knee is affected, the assessment of the outcomes will relate to this knee. If the patient has two affected knees and only one meets the ACR criterion, only this knee will be evaluated. In the case that both knees are affected following the inclusion criteria, the more painful knee will be chosen for evaluation.

#### Primary outcome

We will use the Western Ontario and McMaster Universities Osteoarthritis Index (WOMAC) [22] as the primary outcome measure. The WOMAC is a valid and reliable self-administered questionnaire that has been used widely in a variety of clinical trials involving patients with KOA. It can be used as an initial assessment of the intensity of pain and functional disability of KOA. The Chinese version of WOMAC consists of 24 items assessing the patients with KOA pain (5 items), stiffness (2 items), and physical function (17 items). Therefore, it can multidimensionally measure pain, stiffness, and physical functional disability [23]. All 24 questions will be listed on a numerical rating scale ranging from 0 (no symptoms) to 4 (maximum symptoms). Doctors need to help patients perform the self-assessment, collect the total score from the 24 questions, and record it. Higher scores indicate more severe symptoms or physical disability. The evaluation will be performed at baseline and weeks 4, 8, and 12 respectively after randomization; then, we will select the evaluation at week 4 as the primary outcome.

#### Secondary outcome

① We will use the Western Ontario and McMaster Universities Osteoarthritis Index (WOMAC) evaluation at weeks 8 and 12 as the secondary outcome measure.② The pain visual analog scale (VAS) [24]: The VAS is an internationally recognized 10-point scale selected to quantitatively evaluate the level of knee pain during the study. It scores from “0 (none),” “about 2 (mild),” “around 5 (moderate),” “almost 8 (severe),” and “nearly 10 (unbearable)” spaced along the continuum. During the experiment, the VAS assessments will be performed at baseline and weeks 4, 8, and 12 respectively by independent assessors who are not involved in acupuncture treatments (asking subjects to indicate the pain intensity at the most painful points during walking and ascending/descending a step and overall).③ Arthritis Quality of Life Measurement Scale Simplified Scale (AIMS2-SF) [25]: We will use the Chinese version of the Arthritis Quality of Life Measurement Scale Simplified Scale by the Fudan University School of Public Health to assess the quality of life. Because this experiment is aimed at KOA patients, 5 items involving hands and arms in the physical dimension of this scale will be removed, and only the remaining 21 items will be used. All items are scored on a scale of 1 to 5, with the total score represented by the sum of 5 dimensions. The higher the score, the better the quality of life. The evaluation will be performed at baseline at weeks 4, 8, and 12 respectively after randomization.④Credibility/Expectancy Questionnaire: The Credibility/Expectancy Questionnaire is a quick and easy-to-administer scale for measuring treatment expectancy and rationale credibility for use in clinical outcome studies [26]. Participants will be asked “How much do you feel acupuncture therapy will help to reduce your symptoms?” at baseline.⑤ Emotional monitoring: Mood changes, such as depression and anxiety, are common concomitant symptoms of KOA. In order to monitor the impact of emotional changes on the condition of KOA, we will use the Beck Anxiety Inventory (BAI) [27] and Beck Depression Inventory (BDI) [28] to evaluate the emotional state of patients in this trial. The evaluation will be performed at baseline and weeks 4, 8, and 12 respectively after randomization.

